### Ethical Consideration

The Medical Research Ethics Committee Brabant in the Netherlands has approved the study protocol (NW2014-36). The Medical Ethics Committees of all participating hospitals assessed and consented the study protocol. This study is registered at ClinicalTrials.gov with the unique identification number NCT04123275.

## Results

The results of this study are expected to be presented at international scientific meetings and published in 2020 or 2021. The study findings will be reported according to the guidelines outlined by the STROBE (STrengthening the Reporting of OBservational studies in Epidemiology) and TRIPOD (Transparent Reporting of a multivariable prediction model for Individual Prognosis Or Diagnosis) statements [26,27].

## Discussion

An accurate and generalizable model that can be used in clinical practice to predict time to death in cDCD donors is currently lacking. This large prospective multicenter study aims to provide a robust multimodal prediction model based on clinical, physiological, and neuroimaging parameters. In addition, it will provide valuable insights into the process of WLST in cDCD donors and its effect on timing of death (and thus donor potential). As such, this study will fill important knowledge gaps in this essential field of health care.

Accurate estimation of time to circulatory death will help clinicians and nursing staff guide grieving family members and improve the ability of medical teams to predict the chances of organ donation. This helps to manage expectations and prevent disappointment in families that are grieving but motivated to donate. In addition, it could aid in the management of organ donation procurement and transplantation team resources.

Many studies that aim to develop a new prediction tool neglect previously published models. Use of earlier data with refinement of existing models leads to more generalizable models that could be used in daily practice. In our study, we will address external validation using a large cohort with the intention to update previously published prediction tools.

Importantly, this will be the first study that extensively describes donor management in combination with end-of-life care and its impact on the timing of circulatory death in potential cDCD donors. We will provide data on the trajectory of such care during the WLST process. Valuable information on the use of sedatives and analgesics and their influence on the dying process will be obtained. Apart from the timing of death, we will also be able to analyze whether differences in end-of-life care affect family consent rates. We will demonstrate the extent of the variability in cDCD donor care.

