**Objective:**

The objectives of this study are the following: (1) to develop a model predicting time to death within 60 minutes in potential cDCD patients; (2) to validate and update previous prediction models on time to death after WLST; (3) to determine timing and patient characteristics that are associated with prognostication and the decision-making process that leads to initiating end-of-life care; (4) to evaluate the impact of timing of family approach on organ donation approval; and (5) to assess the influence of variation in WLST processes on postmortem organ donor potential and actual postmortem organ donors.

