## Introduction

### Background

There is a worldwide shortage of deceased organ donors. Controlled donation after circulatory death (cDCD) is an increasing source of organs for transplantation. In the Netherlands, 59% of the effectuated postmortem organs were from cDCD donors. An increasing number of countries worldwide are establishing a cDCD program. The proportion of organ donations from cDCD donors compared to brain death donors is projected to increase in the upcoming years [1].

However, there are major challenges specific to the cDCD program. First, these patients are not brain-dead and organ donation can only occur after circulatory death (cardiac arrest). As such, withdrawal of life-sustaining treatment (WLST), including stopping mechanical ventilation, should occur to allow circulatory arrest. The time between WLST and circulatory arrest determines whether organs can be donated or not. In most countries, this time is set at a maximum of 1 or 2 hours to preserve organ quality for transplantation purposes. If patients do not arrest within this time frame, organ donation cannot occur. One of the hurdles of cDCD donations is to predict which patients will arrest within the specific time frame. This directly affects family guidance as the treating team and families have to manage family expectations, especially when failure to donate occurs because patients do not arrest within the specified time frame after WLST. Finally, inaccurate prediction of time to circulatory death also influences efficient utilization of the organ procurement and transplantation teams; after WLST is started, these teams need to be fully prepared and present in the operating room to manage recovery and transplantation of organs if the potential donor dies within the given time frame [2].

Factors associated with early circulatory arrest after treatment withdrawal include a younger age, being on artificial ventilation without spontaneous triggering by the patient, needing a high percentage of oxygen, the use of vasopressors, the absence of brain stem reflexes, and a low arterial pH [3]. Interestingly, there are studies that suggest that the use of analgesics or sedatives does not significantly influence the timing of death [4-6].

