Necessary steps to be taken before the initiation of a cDCD procedure are as follows: prognostication, making the decision to withdraw life-sustaining treatment, and approaching family and obtaining their consent for organ donation. Initiation of end-of-life care in acute settings and inexperience in organ donation practices outside ICUs have a negative impact on the number of potential donors [19,20]. Postponing the discontinuation of medical treatment gives professionals more time to guide families adequately and inform them about the dying process and organ donation [21]. Data collected about end-of-life decision-making can provide more insight into whether a patient may be eligible for a cDCD procedure based on time to circulatory death. Such insight can be useful when giving grieving families estimations of time to death and the likelihood that a donation procedure could be performed. However, studies on this important topic are lacking.

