### Data Collection and Management

Data will be prospectively collected by the local investigators, supported by a research manager (International Organization for Standardization certified), and recorded using a web-based electronic case report form (eCRF). The variables will be obtained from the electronic medical records of the following hospitals: Radboudumc Nijmegen, Erasmus University Medical Center Rotterdam, University Medical Center Groningen, Isala Hospital Zwolle, Jeroen Bosch Hospital ’s-Hertogenbosch, and Elisabeth-Tweesteden Hospital Tilburg. Before inclusion, all local investigators received detailed written instructions and on-site training regarding the completion of the eCRF. In addition, the lead investigator team will have regular site visits to perform random sample checks on patient files and data entry. The primary investigator has access to the encrypted data. The primary investigator reviews all incoming data for accuracy and completeness. The research manager can generate data queries and provide trailing records on adjustments of data entered. After completion, the data will be exported in SPSS files (IBM Inc) for further analysis.

A preceding pilot analysis with retrospectively collected data was performed. Two different retrospective data sets were created. One included data from a single hospital (Elisabeth-Tweesteden Hospital, Tilburg, the Netherlands) with a neurosurgical and traumatology focus [23]. The second data set included nationwide demographic data from 2014 to 2016 of all cDCD donors that did not arrest within the set time frame of circulatory arrest of 120 minutes. Anonymized data were provided by the databases of the Dutch Transplant Foundation [24]. Apart from discussion within our own research group, previously published prediction models and analysis of these two data sets contributed to the assessment of key variables to be collected, refinement of the eCRF, defining the appropriate prediction models on time to death for external validation, and providing insight in the donor potential pool after 2, 3, and 4 hours.

Variables to be collected are summarized in Multimedia Appendices 1 and 2. Diagnosis on admission will be classified according to the International Statistical Classification of Diseases and Related Health Problems by the World Health Organization (WHO), tenth revision (ICD-10). Variables related to end-of-life care are shown in Textbox 1.

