Parameters to be collected during and after withdrawal of life-sustaining treatment (WLST).Withdrawal of mechanical ventilationRemoval of endotracheal or tracheostomy tubeAfter endotracheal or tracheostomy tube removal: insertion of an oropharyngeal airway, suction of secretions, lateral decubitus positioning, oxygen administrationType and dose of medication administered for palliative care purposes

Variables on neurologic examination; physiological variables; and dose of sedation, analgesia, and vasopressors will be evaluated at 3 time points (1) at time of end-of-life decision-making of the medical team, (2) 30 minutes before WLST, and (3) at 1 time point after WLST until circulatory arrest (Multimedia Appendix 3).

Additionally, the computed tomography (CT) images of the brain of all included patients at admission and the last brain CT prior to WLST will be evaluated using a standardized blinded approach by a neurologist and neuroradiologist. The location and size of brain disorders, magnitude of brain shift, and presence of hydrocephalus will be assessed.

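### End-of-life care items recorded during and after withdrawal cannot be causes of family consent, and consent may confound the actual-donor outcome of objective 5

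*Protocol article*

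**What the plan says.** The Discussion, after describing the care and medication to be documented around withdrawal, adds family consent as a further outcome: "we will also be able to analyze whether differences in end-of-life care affect family consent rates".

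Data Collection and Management tells the reader which variables count as end-of-life care: "Variables related to end-of-life care are shown in Textbox 1". The box opens with "Parameters to be collected during and after withdrawal of life-sustaining treatment (WLST" and lists withdrawal of ventilation, tube removal, airway care and positioning after tube removal, and the type and dose of palliative medication.

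The Background sets out the sequence: "Necessary steps to be taken before the initiation of a cDCD procedure are as follows: prognostication, making the decision to withdraw life-sustaining treatment", followed by "approaching family and obtaining their consent for organ donation". It also says of the recovery and transplantation teams that "after WLST is started, these teams need to be fully prepared and present in the operating room".

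Two other statements bear on the point. The Abstract (objective 4) and the Objectives section define the consent question by the timing of the family approach. Objective 5 in the Abstract is "to assess the influence of variation in WLST processes on postmortem organ donor potential and actual postmortem organ donors".

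**The concern.** An exposure can affect an outcome only if it comes first. The items that the article labels as end-of-life care are recorded once withdrawal is under way, when the family's answer on donation should already be known. Using them to explain consent would reverse the order of events.

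The opposite direction is plausible. A patient whose family has agreed undergoes withdrawal inside a donation procedure with teams standing by; a patient whose family has refused does not. If this alters how withdrawal is carried out, the items will be associated with consent without having influenced it.

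The same path could reach objective 5. The cohort is every eligible potential donor, and objective 4 studies approval, so it contains refusals. Refused patients cannot become actual donors. A withdrawal practice that is merely more common after consent would then seem to raise donor numbers.

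Conclusions that certain withdrawal practices change consent or the number of donors could influence care at the end of life, so the direction of the association matters.

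**Working it through.** The plan has no figure to reproduce here. The check sets the stated timings side by side.

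**Order of events for one patient**

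| Step | Source | Recorded then |
|---|---|---|
| End-of-life decision | Data Collection and Management, time point 1 | Neurological and physiological variables; sedation, analgesia and vasopressor doses |
| Family approach and consent | Background, steps before a cDCD procedure | Timing of approach and approval (objective 4) |
| 30 minutes before WLST | Data Collection and Management, time point 2 | Same variables as time point 1 |
| WLST and afterwards | Textbox 1; time point 3 | Ventilation withdrawal, tube removal, airway care, palliative medication |

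The Background list supports placing time point 1 before the family approach, but the article does not state that order outright.

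**Which exposures can precede consent**

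- Timing of the end-of-life decision and of the family approach: yes.
- Time point 1 characteristics and doses: yes, on the order above. The article confirms that "dose of sedation, analgesia, and vasopressors will be evaluated at 3 time points (1) at time of end-of-life decision-making of the medical team".
- Time point 2 variables: not established, since consent may already have been given 30 minutes before WLST.
- Textbox 1 items: no, for any patient whose family answered before WLST.

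**Which exposure the Discussion sentence means**

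Data Collection and Management attaches the term to Textbox 1. The nearby Discussion sentences concern the course of care during WLST and the effect of sedatives and analgesics on dying. The consent sentence then moves on from timing of death to a second outcome. That context points to the Textbox 1 exposure.

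**Objective 5**

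For any WLST item, because refused patients contribute no donors:

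P(donor | item) = P(consent | item) × P(donor | consent, item)

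Suppose the item has no effect on donation, so that the last factor equals d whether or not the item was used. Then:

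- Whole cohort: ratio of donor proportions = P(consent | item) / P(consent | no item). This differs from 1 whenever use of the item differs by consent status.
- Consented patients only: ratio = d / d = 1.

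**Size**

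The article gives no consent rate and no frequency of any WLST item by consent status, so the bias cannot be sized. With purely hypothetical inputs, fixing use at 50% among refused patients, the odds ratio between item and consent under no true effect would be:

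- 50% use among consented: (0.5/0.5)/(0.5/0.5) = 1.0
- 60%: (0.6/0.4)/(0.5/0.5) = 1.5
- 80%: (0.8/0.2)/(0.5/0.5) = 4.0

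These figures show only that an assumed difference in practice passes straight into the association. They are not evidence about this study.

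**The case against.** The strongest reply is that this is one forward-looking sentence in a Discussion. The Statistical Analysis section specifies no consent model, and the details of a secondary analysis belong to a fuller document that is not shown. The formal consent objective uses the timing of the family approach, which precedes the answer. This stands. A reader might infer that the plan as a whole analyses consent backwards, or that the study will report reverse causation as an effect. The article does not support either reading; it supports a risk, confined to the Textbox 1 items.

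A second reply is that end-of-life care is used more broadly elsewhere. The Background discusses starting such care in acute settings and delaying withdrawal so that families can be guided, and drug doses are recorded at the end-of-life decision. Multimedia Appendices 1 to 3, which hold the variable lists and time axis, are not shown. This stands as a limit: it cannot be claimed that every care variable follows consent. It does not remove the problem, because the only place where the article defines the end-of-life care variables points to Textbox 1.

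Third, a comparison of consent rates between hospitals with different usual practice would not be reversed in the same way. That is true, but there are only six hospitals, and the teaching hospitals were chosen for their differing specialties, so case mix would confound the comparison.

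Fourth, on objective 5, the Objectives section describes an effect through timing of death, donor potential does not require consent, and nothing in the article shows that WLST practice differs by consent status. This also stands, so the confounding must be stated conditionally. Even so, the Abstract names actual donors as an outcome, and refused patients contribute none.

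**Conclusion.** The point holds in limited form. For the Textbox 1 items, the Discussion's proposed analysis of consent has the wrong time order and risks presenting reverse causation as an effect. Two things are not affected in this way: the stated objective on timing of the family approach, and the drug doses recorded at the end-of-life decision. For objective 5, consent would confound the actual-donor outcome if WLST practice differs by consent status; the article makes this plausible but does not show it.

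The conclusion rests on two assumptions: that the Discussion sentence uses the term as Data Collection and Management defines it, and that refusals, like consents, are known before WLST. The Background states the order only for patients entering a cDCD procedure. No magnitude can be given. The 60-minute prediction model and the external validation of earlier models are untouched, so this is a correction to secondary analyses.

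**What to change.** 1. Reword the Discussion sentence to match the consent question in the Objectives section, the timing of the family approach.
2. In any consent analysis, admit only exposures that precede the family's decision: timing of the end-of-life decision, timing of the family approach, and time point 1 characteristics and doses. If the time of the family's answer was not recorded, the time of the approach is a safe cut-off, since the approach comes before the answer.
3. Report Textbox 1 items by consent status descriptively only, without wording that implies an effect on consent.
4. For objective 5, assess actual donors among consented patients, and stratify or adjust the analysis of WLST practice and time to death for consent status.

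Consent status is already needed for objective 4, so the change is one of wording and analysis. The cost is a smaller denominator for the actual-donor analysis. By how much cannot be said, because the article gives no expected consent rate for its 400 patients.

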## Appendix

Multimedia Appendix 1 Overview of demographic, clinical, and neurological parameters to be collected from potential cDCD donors. cDCD: controlled donation after circulatory death.

Multimedia Appendix 2 Overview of ventilatory, hemodynamic, and pharmacological parameters to be collected from potential cDCD donors. cDCD: controlled donation after circulatory death.

Multimedia Appendix 3 Axis showing the corresponding parameters to be collected per time point.

Multimedia Appendix 4 Peer reviewer report from the Dutch Transplant Foundation.

## Abbreviations

AUC: area under the curve
cDCD: controlled donation after circulatory death
CT: computed tomography
eCRF: electronic case report form
ICD-10: International Statistical Classification of Diseases and Related Health Problems by the World Health Organization (WHO), tenth revision
ICU: intensive care unit
LASSO: least absolute shrinkage and selection operator
STROBE: STrengthening the Reporting of OBservational studies in Epidemiology
TRIPOD: Transparent Reporting of a multivariable prediction model for Individual Prognosis Or Diagnosis
WLST: withdrawal of life-sustaining treatment
